### Statistical analysis

**Study 1** Both non-inferiority and superiority analyses will be conducted. For non-inferiority analyses, if the non-inferiority null hypothesis is to be rejected, the upper limit of the CI around the observed difference should be less than the non-inferiority margin. Multi-level, mixed-effects generalised linear model analyses will be used to construct the 95% CIs that compare effectiveness and safety outcomes between groups. These models will nest patient admissions within wards, treating both as random factors, to account for the clustered nature of these data. Weekend allied health service delivery model provided will be treated as a fixed factor. The distribution of the length of stay outcome will be examined ( $\pm$  transformations as indicated) as a part of model building as these data are commonly skewed. Data from

**Table 3 Outcome of power analysis for three outcomes for each study at each site (assuming six wards per site), and for both sites combined**

| Outcome                                                                                | Proportion 1
(weekend allied
health services) a | Proportion 2
(no weekend allied
health services) | Single site
or both
sites combined | Assumed
coefficient
of variation | Assumed
number of
patients per
study | Power |
|----------------------------------------------------------------------------------------|------------------------------------------------------------------|--------------------------------------------------------|------------------------------------------|----------------------------------------|-----------------------------------------------|-------|
| Proportion of patients who stay longer than their AR-DRG average inlier length of stay | 0.40                                                             | 0.42                                                   | Single                                   | 0.4                                    | n = 7,000 b                        | 0.65  |
| Proportion of patients who are readmitted within 28 days                               | 0.10                                                             | 0.12                                                   | Single                                   | 0.4                                    | n = 7,000 b                        | 0.96  |
| Proportion of patients who experience at least one of the adverse events listed        | 0.10                                                             | 0.12                                                   | Single                                   | 0.4                                    | n = 7,000 b                        | 0.96  |
| Proportion of patients who stay longer than their AR-DRG average inlier length of stay | 0.40                                                             | 0.42                                                   | Both                                     | 0.4                                    | n = 14,000 b                       | 0.99  |
| Proportion of patients who are readmitted within 28 days                               | 0.10                                                             | 0.12                                                   | Both                                     | 0.4                                    | n = 14,000 b                       | >0.99 |
| Proportion of patients who experience at least one of the adverse events listed        | 0.10                                                             | 0.12                                                   | Both                                     | 0.4                                    | n = 14,000 b                       | >0.99 |

AR-DRG, Australian Refined Diagnosis-Related Group.

aBaseline proportions based on data drawn from administrative datasets at participating sites covering a 12-month period.

bNote that for the single site analyses we assume there will be 7,308 per study, but use only 7,000 in the power analysis to allow for loss of patients during the transition phases between intervention and control conditions and for transfers between study wards. Correspondingly, we use 14,000 when considering the power of both sites combined.

patients who are exposed to both control and intervention conditions within each study will be excluded from the analyses. Analyses will be adjusted for index study ward (first study ward the patient was admitted to during that inpatient episode of care), calendar time using each step in the wedge design as a categorical covariate and for historical data collected for the outcome being examined from each site over the previous 2 years mapped against these steps to account for potential local seasonal variations in the outcomes collected.

Analyses will be conducted at a site-level with pre-planned meta-analyses across both sites using patient-level data from phase 1 and separately for phase 2. These meta-analyses will examine the main effect of the usual care weekend allied health service as opposed to the control condition across sites. A site-by-intervention interaction effect will also be examined to determine if there is heterogeneity in results between sites. This is plausible as a dose-response relationship may exist between the amount of resource allocated to the weekend allied health service and the study outcomes. In this study, local data collected prior to the study indicated that Dandenong Hospital allocated approximately four times as much resource to the acute medical and surgical wards participating in this research. Meta-regression will be employed using ward-level data, treating each ward over time as a pre-post intervention study to identify if the labour costs consumed on each ward for provision of the weekend allied health service explains variation in the change in each outcome within ward.

Patients who are exposed to both intervention and control conditions will be excluded from analyses to minimise potential contamination that is made possible by having the transition periods within the stepped wedge design.

**Study 2** These analyses will be equivalent to the analyses conducted for study 1; however, non-inferiority analyses will not be conducted for this study.

A grand meta-analysis is planned, pooling results between studies 1 and 2 to examine whether there is a significant study-by-intervention interaction effect. This analysis will examine whether the effect of the stakeholder-driven model of weekend allied health service was significantly different to that of the usual care weekend allied health service delivery model.

Sensitivity analyses will be conducted if there are unit closures (for example, surgical unit closures over the Christmas holiday period) that are likely to affect the caseload on related wards at these times. Data within these cells of the stepped wedge design will be treated as missing in the sensitivity analyses.

**Economic analysis** The primary economic analysis will be a cost-effectiveness analysis from the hospital perspective that examines the incremental cost per patient admitted. These costs will include the 'total cost' of patients during their admission plus additional costs from an unplanned admission within 28 days. Data from patients who are transferred between wards in different study periods (that is one without access to allied health services, one with access to allied health services) will be excluded from the analyses as will data from patients who remain within the same ward over two or more weekends if they are allowed to access weekend allied health services during one weekend, and not allowed to access allied health services on another. Secondary economic evaluations will examine the incremental cost per difference in clinical outcome for the measures of functional independence (studies 1 and 2) and health-related quality of life (study 2).

**Qualitative data analysis** Both content and thematic analysis will be used for the analysis of qualitative data collected as a part of this study [38].

**Analysis of workforce absenteeism outcome** It was initially planned to analyse these data in a similar manner to other outcomes; however, it has become apparent that for some professional groups, staff operate over multiple wards that may be in the intervention or control periods during the study. Hence, we will only compare data collected from the first and last months of each study when all wards within the study are either completely in control or intervention periods.

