#### **Primary outcome measure: 1) length of stay**

Mean overall length of stay per patient who is treated on one of the targeted wards will be used as the primary outcome. This measure is often used as an indicator of hospital efficiency [26]. Length of stay is the key overall driver of inpatient costs and is the most readily available outcome to enable stopping rules to be checked during study 1. However, overall mean length of stay is limited as an outcome for this project as: i) these data can be skewed by highly influential outliers, ii) length of stay of longer-stay patients will not be known until they are

discharged (thus interim analyses for non-inferiority to check stopping rules may underestimate mean length of stay) and iii) patient admission casemix profile may vary over the study period (for example, a study ward may start admitting more patients who typically stay longer). To account for these limitations, we will also examine the proportion of patients who stay longer than their Australian Refined Diagnosis-Related Group average 'in-liner' length of stay according to data published from the previous year [27].

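### The planned mixed model has no ward-by-month term, so if outcomes vary by ward-month its 95% CIs are too narrow and false non-inferiority exceeds 2.5%

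*Protocol*

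**What the plan says.** All of this is in the Protocol, Statistical analysis, Study 1, unless another section is named. Study 2 is to be analysed equivalently, without the non-inferiority part.

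- **Intervals:** "Multi-level, mixed-effects generalised linear model analyses will be used to construct the 95% CIs".
- **Random part:** "These models will nest patient admissions within wards, treating both as random factors, to account for the clustered nature of these data".
- **Service effect:** "Weekend allied health service delivery model provided will be treated as a fixed factor".
- **Time:** one adjustment is "calendar time using each step in the wedge design as a categorical covariate", which gives a single effect per step for all wards in the analysis. A second adjustment, described by site, uses "historical data collected for the outcome being examined from each site over the previous 2 years mapped against these steps".
- **Ward:** "Analyses will be adjusted for index study ward", defined as the first study ward of the inpatient episode.
- **Decision rule:** for non-inferiority, "the upper limit of the CI around the observed difference should be less than the non-inferiority margin". The margins, in Trial safety, are 1 day for mean length of stay and 0.02 for the proportions.
- **Change over time within a ward:** the section on length of stay warns that "a study ward may start admitting more patients who typically stay longer". The sensitivity-analysis paragraph foresees unit closures that alter the caseload of related wards at particular times.

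**The concern.** A model with a single ward effect treats two patients on the same ward as equally alike whether they were admitted in the same month or six months apart. It also assumes that all wards follow the same time course. The participating wards range from orthopaedic surgery and stroke to respiratory medicine and general surgery, so a common time course is a strong assumption.

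In a stepped wedge the service contrast is made between ward-months. If one ward has a run of unusual months, that goes into the estimated service effect. The model reads it as independent patient-level noise and divides it by the number of patients. The interval is then too short.

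That interval decides both non-inferiority and superiority. In study 1, an error in this direction favours concluding that withdrawing a service is acceptable.

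**Working it through.** **No figure to reproduce.** The protocol gives no ward-month variance, intra-cluster correlation or error rate for this model. Table 3 is used here only for its rates, coefficient of variation (CV) and numbers. Its power values play no part in the ratio below.

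**Inputs**
- Admissions per site used in the power analysis: 7,000 (Table 3, note b). Six wards × 7 months = 42 ward-months, and 7,000/42 = 167 per ward-month. The unreduced figure in the Group 1 section is 174.
- Baseline rates 0.40 (stay beyond the AR-DRG inlier average) and 0.10 (readmission, adverse events), with CV 0.4 (Table 3).
- rho, the ward-month share of (ward-month + patient) variance: **assumed**.

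**Formula.** Let s² be the patient-level variance, g the ward-month variance and n the admissions per ward-month. After ward and step are removed, a ward-month mean has variance s²/n + g. The planned model counts only s²/n. With g/s² = rho/(1 − rho),

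true SE / model SE = r = sqrt(1 + n·rho/(1 − rho)).

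With the true difference exactly at the margin, a nominal 95% interval falsely declares non-inferiority with probability Φ(−1.96/r). Its coverage is 2Φ(1.96/r) − 1. Neither depends on the size of the margin, so this also covers length of stay, for which no SD is given. The formula is exact for a linear analysis of ward-month means with ward effects removed. For other link functions it is an approximation.

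| rho (assumed) | r | coverage | false non-inferiority |
|---|---|---|---|
| 0 | 1.00 | 95% | 2.5% |
| 0.0005 | 1.04 | 94% | 3.0% |
| 0.001 | 1.08 | 93% | 3.5% |
| 0.005 | 1.36 | 85% | 7.4% |
| 0.01 | 1.64 | 77% | 11.6% |

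**Tied to the protocol's CV.** The between-ward variance is (0.4 × 0.40)² = 0.0256 for the 40% outcome and (0.4 × 0.10)² = 0.0016 for the 10% outcomes. The same assumed shares of it are taken as month-specific for both:

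- 40% outcome, s²/n = 0.24/167 = 0.00144.
  - 5% share: g = 0.00128, r = sqrt(1 + 0.00128/0.00144) = 1.37, false non-inferiority 7.7%.
  - 10% share: g = 0.00256, r = 1.67, false non-inferiority 12.0%.
- 10% outcomes, s²/n = 0.09/167 = 0.00054.
  - 5% share: g = 0.00008, r = 1.07, false non-inferiority 3.4%.
  - 10% share: g = 0.00016, r = 1.14, false non-inferiority 4.3%.
- 1% share: 3.5% for the 40% outcome and 2.7% for the 10% outcomes.

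In plain units, the 5% and 10% shares for the 40% outcome mean that a ward's monthly rate varies with an SD of 3.6 and 5.1 percentage points beyond sampling error.

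**Checks**
- The exact variance of the random-ward estimator gives nearly the same ratios for six wards: 1.37 and 1.66 for the 40% outcome, 1.07 and 1.13 for the 10% outcomes. They are the same for 12 wards.
- Random-ward models were fitted by REML to simulated six-ward trials, 600 runs per setting. With no ward-month variance, the planned structure covered 94 to 95%, with false non-inferiority of 2.2 to 2.7%.
- In the same simulations, a ward-month term kept coverage at about 93 to 96% when ward-month variance was present.

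**The case against.** The strongest objection is that the size rests entirely on a variance the protocol does not report. This stands. At the low end the effect is negligible, and for the 10% outcomes it is modest at the shares used here. The larger figures for the 40% outcome need monthly swings of 3.6 to 5.1 points, about twice the 0.02 margin.

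The casemix warning is also weaker evidence than it looks. It concerns mean length of stay and says only that casemix may vary. The AR-DRG-referenced outcome was added to deal with that limitation, so casemix is a poorer reason for drift in the 40% outcome. It still makes ward-specific change plausible in general, as does the provision for unit closures.

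A reader might draw three stronger conclusions that the protocol does not support:

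- *That the intervals are certainly too narrow.* They are so only if ward-month variance exists. Without it the planned model holds its level.
- *That six wards per site is the cause.* The ratio is the same with 12 wards. It grows with admissions per ward-month, so pooling the two sites does not remove it.
- *That ward is fitted twice, as random factor and as covariate.* The index-ward wording may only say which ward a transferred patient is counted under. It is an ambiguity to clear up, not a demonstrated error.

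The choice of small-sample correction could properly be left to an SAP. The random structure is different, because the protocol states it and leaves this term out.

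**Conclusion.** The point holds in conditional form. The stated model leaves no room for ward-specific month-to-month variation, and the protocol gives reasons to expect some. If it is present, the 95% CIs are too narrow by the factor derived above.

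Over the assumed range of rho from 0.0005 to 0.01, one-sided false non-inferiority runs from 3.0% to 11.6% against 2.5%. At the protocol's CV of 0.4, with 5 to 10% of ward variance month-specific, it is about 8 to 12% for the 40% outcome and 3 to 4% for the 10% outcomes. Superiority intervals lose coverage in the same way.

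The omission should be corrected because the remedy is cheap and the error favours withdrawal of a service. The documents do not allow a statement that the trial's conclusions will be wrong.

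**What to change.** 1. Add a random ward-by-step effect to every primary model: site-level and pooled, studies 1 and 2. Use a small-sample reference suited to the model type. Kenward-Roger and Satterthwaite belong to linear mixed models and need an approximation for binary or rate outcomes. Alternatively, analyse at ward-month level with a t reference. The small number of wards matters for this reference once the term is in the model.
2. State whether index ward is the random factor itself or a separate covariate.
3. If a permutation check is added, use the actual number of orders: 6! = 720 for a six-ward site, and 5! = 120 for Western Hospital in study 2, which has five wards. For non-inferiority, shift the null to the margin. A test of no effect does not check that claim.

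The cost is a change of wording in the protocol and SAP, with no new data. Intervals become wider if ward-month variance exists, and little precision is lost if it does not.

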#### **Group 1**

'All patients on participating wards.' This group will consist of patients admitted to acute medical or surgical wards involved in the trial who are over the age of 18 years. Paediatric patients will be excluded from this study as they are not routinely seen on the selected wards (none are paediatric units or have paediatric beds) and have different provisions for service delivery. It is anticipated, based on previous patient flow data, that each ward will have an average of 174 patient admissions per month during the trial. This means that 6 wards at 1 site will have 7,308 patient admissions during the 7 months of study 1 and 7,308 during the 7 months of study 2. This will lead to an anticipated total of 29,232 patient admissions during the overall study period.

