### **Trial safety**

The process of disinvestment in allied health services has the potential to be detrimental to patient safety and/or organisational outcomes. The checking of stopping rules and development of clinical exceptions will, therefore, be used to ensure safety. A stopping rule allows data to be monitored and the trial to be stopped if there is evidence of a lack of safety or efficacy associated with the intervention [34]. During study 1, interim analyses will be conducted monthly to ensure that patient outcomes have not dropped below a pre-specified non-inferiority margin. This margin represents the maximum amount of gain anticipated if the amount of resources being saved were to be reallocated to another purpose. Discussion groups with clinicians and project investigators initially determined that the non-inferiority margin should be 0.8 multiplied by the standard deviation of the targeted outcome. This is equivalent to 'Cohen's large effect size' [35]. However, review of the standard deviations for the outcomes that these stopping rules would be applied to revealed that these margins were too wide to be acceptable to the management of participating hospitals. As a result of these consultations, the following stopping rules were developed:

1. The 95% CI of the effect (difference between means) of having no weekend allied health services exceeding a 1-day increase in mean length of stay.
2. The 95% CI of the effect (difference between proportions) of having no weekend allied health services exceeding an absolute change of 0.02 (2%) in the outcomes of the proportion of patients who stay longer than their average inlier Australian Refined Diagnosis-Related Group (ARD-RG), the proportion of patients who experience one or more of the previously specified adverse events, or the proportion of patients who are unexpectedly readmitted within 28 days.

Management at each site also reserved the right to review other study data (for example, the proportion of patients discharged on the weekend) in determining whether the study should continue at each site. Interim analysis will be conducted during each month of study 1 and reported back to the project executive committee.

The project executive committee will then forward their recommendations along with blinded data to an independent data-monitoring committee at each site to make a determination as to whether the project should be ceased on the basis of the analysis conducted.

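### Excluding patients exposed to both conditions selects on length of stay, so it biases that primary outcome by an amount that depends on a stay distribution and a dating rule the protocol does not give

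*Protocol*

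**What the plan says.** The Protocol's Statistical analysis section states under Study 1 that "patients who are exposed to both control and intervention conditions within each study will be excluded from the analyses". It repeats the rule later in the same section and gives contamination as the only reason: these patients "will be excluded from analyses to minimise potential contamination that is made possible by having the transition periods within the stepped wedge design". The Study 2 analyses are to be equivalent apart from non-inferiority. The Economic analysis paragraph drops patients transferred between wards under different conditions, and also "data from patients who remain within the same ward over two or more weekends" when those weekends fall under different conditions. That is the only working definition of mixed exposure; none is given for the clinical outcomes.

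The planned models adjust for index ward, for step as a categorical covariate and for historical data. The Trial safety section sets the bounds. For stay the bound is the 95% CI of the effect of "having no weekend allied health services exceeding a 1-day increase in mean length of stay". For the proportions, including stay beyond the AR-DRG inlier average, it is an absolute change of 0.02.

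The only consequence of exclusion that the protocol recognises is lost numbers: Table 3, note b, goes from 7,308 to 7,000. The limitations listed for length of stay (outliers, undischarged patients, casemix) do not include this selection. The protocol gives no mean or SD of stay, and does not say whether admission or discharge date sets a patient's step.

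**The concern.** A patient can be exposed to both conditions on a ward only by being in hospital when that ward switches, and long-stay patients are far more likely to be there than short-stay patients. The exclusion is therefore made on the outcome.

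It is also one-sided. If steps are set by admission date, every straddler belongs to a cell before the switch, mostly the last one, and no cell after the switch loses anyone. If steps are set by discharge date, the first cells after the switch are depleted instead. Because the depleted cell falls in a different month for each ward, neither a ward effect nor a step effect absorbs it.

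At stake are the study 1 non-inferiority conclusion on mean stay, the AR-DRG exceedance outcome, the cost analysis and the comparison of the two service models. Before the switch means service in study 1 and no service in study 2. The same selection therefore pushes the service-minus-no-service effect in opposite directions in the two studies, and the planned study-by-intervention term picks up the sum. If the monthly interim checks use the same exclusion, which the protocol does not say, they would be affected too.

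**Working it through.** **Inputs from the protocol.** The Group 1 section says "each ward will have an average of 174 patient admissions per month during the trial" and "6 wards at 1 site will have 7,308 patient admissions during the 7 months of study 1". The figure reproduces: 174 × 6 × 7 = 7,308. One ward switches per monthly step. The margins are 1 day and 0.02.

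**Assumed.** Mean stay 3 to 8 days, coefficient of variation (CV) 0.7 to 1.5, a 30-day month (174/30 = 5.8 admissions a day), and a true effect of zero.

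**How much of a depleted cell reaches the estimate.** Number the wards i = 1 to 6 by switching order and the steps j = 1 to 7, with condition = 1 when j > i. With ward and step effects, the estimator weights each cell by its residual: condition − (7 − i)/7 − (j − 1)/6 + 0.5.
- Sum over the six last pre-switch cells (j = i): −21/7 − 15/6 + 3 = −2.5.
- Denominator, the sum over the 21 post-switch cells: 21 × 1.5 − 91/7 − 91/6 = 3.333.
- A deficit of one day in every last pre-switch cell therefore shifts the effect by 2.5/3.333 = 0.75 day. With five wards and six steps the factor is 2/2.333 = 0.86.

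**Size of the deficit, exponential stay with mean m.** About m/30 of the last pre-switch month straddles, and those patients' stays average 2m. The remaining mean is (m − 2m²/30)/(1 − m/30), so the deficit is m²/(30 − m).
- m = 3: 9/27 = 0.33, × 0.75 = 0.25 day.
- m = 5: 25/25 = 1.0, × 0.75 = 0.75 day. Exclusions: 6 × 174/6 = 174 of 7,308, or 2.4%.

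Simulation of the full design gives 0.25 and 0.72 day. The approximation ignores stays longer than a month and unequal cell sizes, so it runs high for longer means.

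**Simulated bias in mean stay (days, after minus before the switch, admission-dated).** The any-day rule excludes every stay across the switch. The weekend rule needs at least one weekend on each side.

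| Assumed stay | Rule | Mean 3 | Mean 5 | Mean 7 |
|---|---|---|---|---|
| Gamma, CV 0.7 | any-day | 0.10 | 0.30 | 0.69 |
| | weekend | 0.03 | 0.19 | 0.55 |
| Exponential, CV 1 | any-day | 0.25 | 0.72 | 1.40 |
| | weekend | 0.12 | 0.50 | 1.11 |
| Lognormal, CV 1.5 | any-day | 0.49 | 1.20 | 2.09 |
| | weekend | 0.31 | 1.02 | 1.82 |

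Separate lognormal runs gave 0.83 to 0.88 (any-day) and 0.59 to 0.65 (weekend) at mean 5, SD 6, and about 1.8 and 1.5 at mean 8, SD 9. Discharge dating gives about the same size with the sign reversed (exponential, mean 5, any-day: −0.73). Keeping everyone gives −0.03 to +0.03 day.

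**Cross-check against the protocol's own allowance.** 7,308 − 7,000 = 308 covers transition and transfer losses together. That is 308/6 = 51 per switch, or 51/174 = 30% of a ward-month. If all were transition losses, mean stay would be about 0.30 × 30 = 9 days (simulated bias about 2.2 days, exponential). If half were, about 4.5 days (about 0.55 day). If a third were, about 3 days (0.25 day).

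**AR-DRG proportion.** The proxy is stay above the 60th percentile, to match the 0.40 baseline. For mean/SD 3/4, 5/6 and 8/9 the any-day rule shifts it by 2.9, 4.5 and 7.6 points, and the weekend rule by 0.8, 2.1 and 4.6. Another coding of the weekend rule gave 1.8, 3.5 and 6.3 points. These fell to 0.9, 2.5 and 4.3 when half the log-variance of stay was assumed to lie between DRGs.

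**Comparison of the two studies.** If both studies had the same stay distribution and design, the biases would add: 2 × 0.72 = 1.4 days for exponential stay with mean 5.

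**The case against.** A reader might infer that the bias is comparable to the 1-day margin whatever the wards' stay. The documents do not support that. They give no mean or SD, and say only that 0.8 SD was judged too wide a margin. With short, low-skew stays the bias is a tenth of the margin or less.

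A reader might also infer that the plan favours one model of care. It does not establish this: the sign depends on a dating rule that is not stated and that an analysis plan could fix. The opposite signs in studies 1 and 2 hold only on the service-minus-no-service scale; measured after minus before the switch, the sign is the same in both.

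Further limits stand. The weekend definition comes from the economic paragraph. The AR-DRG shift depends on DRG structure that cannot be recovered from the protocol. The cost bias follows from the same exclusion but has not been calculated. Exact doubling needs similar stay distributions and designs, whereas study 2 has five wards at one site and an expected casemix change. The plan also allows a transformation, so the reported scale may not be days; a log scale does not remove the bias, though (geometric ratio about 1.05 to 1.20 at means of 5 to 7 days, any-day rule).

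Finally, the exclusion has a legitimate purpose. Keeping straddlers mixes exposures and dilutes the effect. The dilution is small: a true 1-day effect would be estimated at 0.94 to 0.99 day.

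**Conclusion.** The rule is wrong as written, for both studies. It conditions on a primary outcome, it acts on one side of each switch, and the ward and step adjustment leaves it in place. This much does not depend on the stay distribution.

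The size does. Against the 1-day margin, the spurious difference in mean stay is about 0.1 day or less at a mean of 3 days with low skew, 0.6 to 0.9 day at a mean of 5 with CV 1.2, and about 1.5 to 2 days at a mean of 7 to 8 with CV above 1. The AR-DRG proportion is biased too, possibly beyond 2 points. Costs would be expected to follow, by an unquantified amount.

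With admission dating, study 1 would make no service look worse and study 2 would make the new service look worse; discharge dating reverses both. Either way the two biases add in the study-by-intervention comparison. The sponsor can settle the size from the 12 months of administrative data behind Table 3.

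**What to change.** In the primary clinical and economic analyses of both studies, keep every admission. Assign its step by admission date and its condition by what was in force on the index ward at admission. Make the both-exposed exclusion a sensitivity analysis, with one definition of exposure for clinical and cost outcomes, and report the number and stay of those excluded on each side of the switch. If a washout is wanted, drop all admissions to a ward in a fixed calendar window before its switch, however long they stayed. A 14-day window of this kind gave a simulated bias of −0.03 day (SE 0.02).

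The cost is a change of wording and a slight dilution towards no difference, since straddlers are about 0.2 to 4% of admissions. In study 1 that dilution leans slightly towards non-inferiority, and the plan should say so.
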